## Abstract

**Objective:**

Family caregivers of people with dementia perform duties that are important for maintaining their loved one's overall well-being. However, it is not yet clear how these caregivers' quality-of-life affects their ability to meet the care demands of their loved ones. The purpose of this study is to utilize a mixed methods approach in investigating how family caregiver quality-of-life affects the care provided to people with dementia. Family caregivers will be recruited from the Rochester, New York area to participate in focus groups or one-on-one interviews. In addition to the qualitative data obtained, caregivers will complete questionnaires regarding their own quality-of-life (e.g., health status, socioeconomic) as well as the care provided to their loved ones with dementia (e.g., how the care provided meets the needs of the care recipient, time spent). A convergent mixed methods approach will be used to analyze the qualitative and quantitative data obtained.

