## Introduction

1

Primary informal caregivers are mainly responsible for the care of people with dementia including Alzheimer's disease (AD). Caregivers perform a variety of duties ranging from shopping for their loved ones' groceries, helping with medications, managing finances and legal affairs, guarding against wandering, and helping with basic and instrumental activities of daily living [1]. However, it is important to note that the caregiving role becomes more demanding as the disease progresses over time, and studies have shown that the quality-of-life (QoL) experienced by dementia caregivers is lower than the QoL of caregivers for persons who do not have this disease [2].

Although several studies have provided evidence for positive aspects of caregiving including lower depression and higher life satisfaction rate, the majority of caregivers find this role to be stressful [2]–[4]. In addition to the stressful nature of caregiving, the care recipient's condition tends to decline over time, making the caregiving role more demanding [5]. This may in turn affect the caregiver's ability to meet their loved ones' care needs, resulting in a decline in the quality of care provided to the care recipient as the disease progresses.

However, there has been no research conducted to directly investigate whether lower caregiver QoL (both pre-existing QoL or changing QoL as a function of caregiving) affects the level or quality of care that caregivers provide to persons with dementia. In a randomized controlled trial assessing the effectiveness of the STrAtegies for RelaTives (START) intervention in the short and long term, the researchers found that an eight-session manual-based coping intervention resulted in decreased anxiety and depression levels for caregivers [6]. Although the researchers also found evidence for improved QoL among caregivers, this did not result in improvement of the QoL of the person living with dementia.

In a published systematic review examining the relationship between caregiver QoL and the quality of care provided [7], we found only one study that was somewhat relevant [8]. However, this single study did not examine the association between QoL and level or quality of care provided to people with dementia. It suggested that the main reason for an absence of research into this topic was the absence of an instrument (i.e. questionnaire) for measuring quality of care provided to care recipients with dementia [7].

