## Materials and methods

2

The study will utilize a convergent mixed methods approach to answer the following research question:

What is the relationship between caregiver quality-of-life and the care provided to persons with dementia?

A convergent mixed methods design involves the collection, analysis, and comparison of both qualitative and quantitative data as part of the same study [9]. To be consistent with this type of mixed methods design, both quantitative and qualitative data will be collected at the same time as part of the same interview session. However, the quantitative and qualitative data will be analyzed separately and the results used to confirm or disconfirm each other [9],[10]. The convergent mixed methods approach also makes it possible to maximize different types of information (for example views of focus group participants and scores from objective questionnaires) to generate results that are richer than what the individual method would have allowed [9],[10].

Further, the convergent mixed methods design permits the efficient collection of data from the same number of participants on both the qualitative and quantitative components since the intent is to make a comparison between the two types of data [9],[10]. Purposeful sampling will be used to select approximately 25 family caregivers from the Rochester, New York area to participate in focus groups or one-on-one interviews (depending on caregiver availability). The sample size of approximately 25 family caregivers selected through this sampling approach will make it possible to collect a sufficient database of qualitative and quantitative information to permit an in-depth understanding of the relationship between family caregiver quality of life and the care provided to people living with dementia [10]. The same participants will be used for both the qualitative and quantitative components of the study. Although caregivers are usually close relatives (e.g., spouses, adult children) of the person with dementia, anyone who provides uncompensated care for at least four hours per week to a person living with dementia will be eligible for inclusion in this study [2].

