Caregiver serving organizations (e.g. Lifespan of Greater Rochester) in the Rochester, New York area will be approached to help identify family caregivers meeting the inclusion criteria. These organizations will send recruitment documents (recruitment letter, e-mail) to potential family caregivers inviting them to participate in the study, and interested participants will be asked to contact the principal investigator (AH). Interviews will take place on-site at the caregiver serving organization's premises and on SUNY Brockport's campus. It should be noted that due to current social distancing restrictions related to the COVID-19 pandemic, focus groups and interviews may be conducted through online video or voice/telephone conferencing. Factors influencing this decision will be made individually with each caregiver participant depending on their access and comfortability with technology. Recruitment materials will include information about preferred options of interaction available to participants. The principal investigator (AH) will facilitate the interviews, and each focus group will have six to eight interviewees [9]. The principal investigator (AH) has extensive experience with focus group interviewing, and has published peer-reviewed studies utilizing qualitative methods [5],[11]. He will note any personal biases or preferences, and will not allow these to affect the research. Each participant will be given a $20 gift card at the end of their interview as compensation for their time and travel expenses. Informed consent will be obtained from participants at the beginning of each interview (focus group or one-on-one). During the focus group interviews, participants will answer questions such as: *Do you receive assistance from other people in providing care for your loved one? Are you always able to meet your loved ones' care needs? etc.*

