## Results and discussion

3

In order to reveal the demographic characteristics of caregivers used in this study (e.g., average age, income, relationship types), descriptive statistics will be computed using data obtained from the interviews and questionnaires. Results from the qualitative and quantitative analyses will identify the components of quality of life that may be important in influencing the care provided by family caregivers. Overall, the study results will help shed light on the relationship between family caregiver QoL and the quality of care provided to people with dementia.

Considering the rapid aging of the U.S. population [1],[2], this study will address an important topic. Once we understand how caregiver QoL affects the care provided to persons with dementia, it will be possible to develop initiatives that better address caregiver needs. These initiatives may include an expansion of respite care for persons with dementia or the provision of specialized training to help caregivers better cope with the impact of the disease on their own QoL. This could ultimately minimize long-term disability and lessen the impact of dementia on the society at large.

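### The purpose and outlook claim that caregiver quality of life affects care, but the questionnaires, taken together in one session, can show only association

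*Protocol article*

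**What the plan says.** The article states its aim in two ways.

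- **Directional.** The Objective in the Abstract speaks of "investigating how family caregiver quality-of-life affects the care provided to people with dementia". Results and discussion expects the results to "identify the components of quality of life that may be important in influencing the care provided by family caregivers", and then continues: "Once we understand how caregiver QoL affects the care provided to persons with dementia, it will be possible to develop initiatives".
- **Associational.** The research question in Materials and methods is "What is the relationship between caregiver quality-of-life and the care provided to persons with dementia". The Results part of the Abstract and the closing sentence of the first paragraph of Results and discussion also speak of a relationship.

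On timing, Materials and methods says that "both quantitative and qualitative data will be collected at the same time as part of the same interview session". Payment follows the same pattern: "Each participant will be given a $20 gift card at the end of their interview". No second measurement, follow-up or comparison group is described. Quality of life is measured with the SF-36, and care with questionnaires on matters such as time spent and how far needs are met.

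The Introduction mentions quality of life that is "both pre-existing QoL or changing QoL as a function of caregiving", and also says that "the care recipient's condition tends to decline over time, making the caregiving role more demanding".

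**The concern.** The directional statements assert more than the research question asks and more than the questionnaires can deliver. If quality of life and care turn out to be correlated, the present wording invites the reader to take this as evidence that quality of life drives care. The article's own Introduction supplies two other explanations: caregiving changes quality of life, and the recipient's decline makes the role harder, which could depress both measures.

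At stake is what the study may conclude. Results and discussion moves from an understood effect to initiatives such as more respite care or caregiver training. If the association arose by one of the other routes, improving caregivers' quality of life need not change the care given. The Introduction itself describes a randomised trial of a coping intervention in which caregivers' quality of life improved but that of the person with dementia did not. That outcome is not quality of care, but it shows why the step from association to effect needs its own evidence.

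**Working it through.** The article gives no effect size, standard deviation or power figure, so there is no figure of its own to reproduce. The check is of what one joint measurement can tell apart.

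**Inputs from the article.** About 25 caregivers in one group; both constructs recorded in one session; significance level 0.05 (two-sided assumed, since sidedness is not stated).

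**Three explanations.** Let Q be the quality-of-life score and C the care score, each standardised. Let e1, e2 and S be independent standard normal variables and b the true correlation.

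1. Quality of life affects care: Q = e1, C = bQ + √(1 − b²)·e2. Then Var(C) = b² + (1 − b²) = 1 and Cov(Q, C) = b.
2. Caregiving affects quality of life: C = e1, Q = bC + √(1 − b²)·e2. By the same steps, Var(Q) = 1 and Cov(Q, C) = b.
3. Shared cause S, such as the recipient's decline: Q = √b·S + √(1 − b)·e1, C = √b·S + √(1 − b)·e2. Each variance is b + (1 − b) = 1 and Cov(Q, C) = √b·√b = b. For a negative correlation, use |b| and reverse the sign of one loading on S.

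All three give the same bivariate normal distribution with correlation b. The likelihood of any data set is the same under each, so the likelihood ratio between any two is 1, whatever b is and however many caregivers are enrolled.

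**Illustration.** 20,000 simulated studies per explanation, n = 25, two-sided 0.05, with b = 0.5 as an assumption:

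| Explanation | Mean r | Share with p < 0.05 |
|---|---|---|
| Quality of life to care | 0.493 | 75.2% |
| Care to quality of life | 0.491 | 74.6% |
| Shared cause | 0.492 | 74.2% |

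The small differences are simulation noise, since the three distributions are identical by the algebra above. A significant correlation is equally likely whichever explanation is true.

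**Is there only one measurement?** The article does not say so in those words. It follows from the single shared session, the single payment at its end, and the absence of any described follow-up.

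**The case against.** The strongest defence is that this is a small, exploratory mixed-methods study whose formal question is already associational. The directional words sit in the purpose and the outlook, one of them is hedged by *may*, and no causal model is planned. Asking caregivers how their own quality of life bears on the care they give is an ordinary qualitative aim, and the two strands are meant to confirm or disconfirm each other. Much of this stands, and it lowers the weight of the point. It does not remove the mismatch: the headline purpose and the basis for the initiatives are still worded as an effect.

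A reader might infer four stronger things that the article does not support.

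- *That the whole design is silent on direction.* The algebra covers the questionnaire strand only. Interviews can yield caregivers' own accounts of what led to what. Such accounts are retrospective, so they suggest mechanisms without establishing time order.
- *That the interview guide lacks suitable questions.* The two questions printed are introduced as examples, and the full guide is not shown. Nothing can be concluded about the rest of it.
- *That the article promises better care or less disability.* The initiatives are described as possibilities, and the disability benefit is put as something that could eventually follow.
- *That the study undertook to separate pre-existing from changed quality of life.* The phrase in the Introduction describes a gap in the literature, not a commitment of this study.

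**Conclusion.** The point holds for the quantitative strand. The purpose and outlook are worded as an effect of quality of life on care, the research question is not, and questionnaire data taken at one time cannot distinguish that effect from the reverse route or a shared cause. The information on direction from a correlation is nil at any effect size and any sample size. The exact identity of the three explanations assumes linear, normal relations. The more general statement, that a correlation is symmetric and carries no time order, does not need that assumption.

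The conclusion also rests on reading the article as describing one measurement per caregiver. It should be corrected because it changes what the study may claim, but it does not invalidate the sampling, the instruments or the planned data collection.

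**What to change.** 1. In the Objective and in Results and discussion, use the wording of the research question. For quantitative results, write *is associated with* in place of *affects* and *influencing*.
2. State once, plainly, that the questionnaire data cannot establish direction.
3. Present the initiatives and the possible reduction in disability as hypotheses for later study, not as following from an understood effect.
4. In the qualitative analysis, code caregivers' accounts by perceived direction: quality of life to care, care to quality of life, or both. If the full guide has no open probes on this, add them. Report the results as perceived mechanisms, not as evidence of temporal order.

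The cost is rewording and a little extra coding, plus any probes that prove to be missing. No added participants, visits or instruments are needed. The downside is a more modest stated conclusion. Keeping the directional aim instead would be a larger change: repeated measurement of quality of life and care, with dementia severity and caregiving load recorded.

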**Results:**

Data from the interviews will be transcribed verbatim and then analyzed qualitatively. Quantitative data from the questionnaires will be analyzed using IBM SPSS Statistics software. A convergent mixed methods approach will be applied to the datasets to help shed light on the relationship between family caregiver quality-of-life and the care provided to people living with dementia. Understanding of this relationship will make it possible to develop initiatives that better address caregiver needs.

## Introduction

1

Primary informal caregivers are mainly responsible for the care of people with dementia including Alzheimer's disease (AD). Caregivers perform a variety of duties ranging from shopping for their loved ones' groceries, helping with medications, managing finances and legal affairs, guarding against wandering, and helping with basic and instrumental activities of daily living [1]. However, it is important to note that the caregiving role becomes more demanding as the disease progresses over time, and studies have shown that the quality-of-life (QoL) experienced by dementia caregivers is lower than the QoL of caregivers for persons who do not have this disease [2].

Although several studies have provided evidence for positive aspects of caregiving including lower depression and higher life satisfaction rate, the majority of caregivers find this role to be stressful [2]–[4]. In addition to the stressful nature of caregiving, the care recipient's condition tends to decline over time, making the caregiving role more demanding [5]. This may in turn affect the caregiver's ability to meet their loved ones' care needs, resulting in a decline in the quality of care provided to the care recipient as the disease progresses.

However, there has been no research conducted to directly investigate whether lower caregiver QoL (both pre-existing QoL or changing QoL as a function of caregiving) affects the level or quality of care that caregivers provide to persons with dementia. In a randomized controlled trial assessing the effectiveness of the STrAtegies for RelaTives (START) intervention in the short and long term, the researchers found that an eight-session manual-based coping intervention resulted in decreased anxiety and depression levels for caregivers [6]. Although the researchers also found evidence for improved QoL among caregivers, this did not result in improvement of the QoL of the person living with dementia.

In a published systematic review examining the relationship between caregiver QoL and the quality of care provided [7], we found only one study that was somewhat relevant [8]. However, this single study did not examine the association between QoL and level or quality of care provided to people with dementia. It suggested that the main reason for an absence of research into this topic was the absence of an instrument (i.e. questionnaire) for measuring quality of care provided to care recipients with dementia [7].

## Materials and methods

2

The study will utilize a convergent mixed methods approach to answer the following research question:

What is the relationship between caregiver quality-of-life and the care provided to persons with dementia?

A convergent mixed methods design involves the collection, analysis, and comparison of both qualitative and quantitative data as part of the same study [9]. To be consistent with this type of mixed methods design, both quantitative and qualitative data will be collected at the same time as part of the same interview session. However, the quantitative and qualitative data will be analyzed separately and the results used to confirm or disconfirm each other [9],[10]. The convergent mixed methods approach also makes it possible to maximize different types of information (for example views of focus group participants and scores from objective questionnaires) to generate results that are richer than what the individual method would have allowed [9],[10].

Further, the convergent mixed methods design permits the efficient collection of data from the same number of participants on both the qualitative and quantitative components since the intent is to make a comparison between the two types of data [9],[10]. Purposeful sampling will be used to select approximately 25 family caregivers from the Rochester, New York area to participate in focus groups or one-on-one interviews (depending on caregiver availability). The sample size of approximately 25 family caregivers selected through this sampling approach will make it possible to collect a sufficient database of qualitative and quantitative information to permit an in-depth understanding of the relationship between family caregiver quality of life and the care provided to people living with dementia [10]. The same participants will be used for both the qualitative and quantitative components of the study. Although caregivers are usually close relatives (e.g., spouses, adult children) of the person with dementia, anyone who provides uncompensated care for at least four hours per week to a person living with dementia will be eligible for inclusion in this study [2].

Caregiver serving organizations (e.g. Lifespan of Greater Rochester) in the Rochester, New York area will be approached to help identify family caregivers meeting the inclusion criteria. These organizations will send recruitment documents (recruitment letter, e-mail) to potential family caregivers inviting them to participate in the study, and interested participants will be asked to contact the principal investigator (AH). Interviews will take place on-site at the caregiver serving organization's premises and on SUNY Brockport's campus. It should be noted that due to current social distancing restrictions related to the COVID-19 pandemic, focus groups and interviews may be conducted through online video or voice/telephone conferencing. Factors influencing this decision will be made individually with each caregiver participant depending on their access and comfortability with technology. Recruitment materials will include information about preferred options of interaction available to participants. The principal investigator (AH) will facilitate the interviews, and each focus group will have six to eight interviewees [9]. The principal investigator (AH) has extensive experience with focus group interviewing, and has published peer-reviewed studies utilizing qualitative methods [5],[11]. He will note any personal biases or preferences, and will not allow these to affect the research. Each participant will be given a $20 gift card at the end of their interview as compensation for their time and travel expenses. Informed consent will be obtained from participants at the beginning of each interview (focus group or one-on-one). During the focus group interviews, participants will answer questions such as: *Do you receive assistance from other people in providing care for your loved one? Are you always able to meet your loved ones' care needs? etc.*

In addition to the qualitative data obtained during these research interviews, caregivers will complete questionnaires regarding their own QoL (for example, health status, employment, etc.) as well as the care (e.g. how the care provided meets the needs of the care recipient, time spent) provided to their loved ones. Family caregiver will complete SF-36, a validated 36-item questionnaire that captures the following eight areas of QoL: vitality, physical functioning, bodily pain, general health perceptions, physical role functioning, emotional role functioning, social role functioning, and mental health [12]. Data from the focus groups and/or interviews will be transcribed verbatim and then analyzed qualitatively by coding the information into major ideas or themes from the perspective of the participants [9]. Quantitative data from the questionnaires will be analyzed using IBM SPSS Statistics version 25 (IBM Corporation, Armonk, NY). The level of statistical significance for the quantitative analysis will be set at p < 0.05. The mixed methods data analysis will involve integrating the qualitative and quantitative results by doing a side-by-side comparison of the two forms of data within the discussion section [9].

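### Both data types come from the same caregivers so that each can check the other, but the integration step makes no stated use of the pairing and no procedure is described that keeps coding independent of the scores

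*Protocol article*

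**What the plan says.** All of the relevant text is in Materials and methods of the protocol article.

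- **Sample.** Purposeful sampling will "select approximately 25 family caregivers from the Rochester, New York area", by focus group or one-on-one interview according to availability. For the groups, "each focus group will have six to eight interviewees".
- **Pairing.** "The same participants will be used for both the qualitative and quantitative components of the study". Both kinds of data are gathered in one session. The design is said to be efficient because equal numbers contribute to each component, "since the intent is to make a comparison between the two types of data".
- **Relation of the two analyses.** "the quantitative and qualitative data will be analyzed separately and the results used to confirm or disconfirm each other".
- **Coding.** Transcripts are "analyzed qualitatively by coding the information into major ideas or themes from the perspective of the participants".
- **Bias.** The principal investigator facilitates the interviews. On his own preconceptions the article says: "He will note any personal biases or preferences, and will not allow these to affect the research".
- **Integration.** The two sets of results are brought together by "doing a side-by-side comparison of the two forms of data within the discussion section".

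Caregivers complete the SF-36 and also answer questionnaire items on how far the care they give meets the recipient's needs.

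**The concern.** The research question concerns a relationship across caregivers: whether those with poorer quality of life provide care that meets needs less well. Paired data can address this person by person. The named integration step sets the results of two separate analyses next to each other in prose, and the article does not say that a caregiver's scores will be read against that same caregiver's account.

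Two things are at stake. First, a low average SF-36 and a common theme of unmet need can both be true of the sample without occurring in the same people. A claim that the strands converge would then say little about the relationship of interest. Second, each strand is given the job of checking the other. That check is worth most if themes are settled without knowledge of the scores, and the article describes no step that secures this. It also states no rule for what counts as confirming or disconfirming, so the decision rests on the authors' judgement when they write the discussion.

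**Working it through.** The article gives no figure for this point that could be reproduced. The check is a reading of its statements against each other, with two small counts.

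**1. Are the data paired?** Yes. The same caregivers supply both types in the same session. The efficiency argument refers to the same number of participants in each component, and a separate sentence says they are the same people.

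**2. Is the pairing used at integration?** No use is stated. The strands are analysed separately, and then the results are compared. The article does not set the level of that comparison. A participant-level reading is possible but not planned in the text.

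**3. What can group results alone show?** Let *a* caregivers out of *n* have low SF-36 scores and *b* voice a theme of unmet need. The number *k* who do both lies between max(0, *a* + *b* − *n*) and min(*a*, *b*). The article gives no values for *a* or *b*, so the following is an assumption for illustration only. Take *n* = 25 and *a* = *b* = 12, the largest equal counts for which *a* + *b* does not exceed 25. Suppose also that every caregiver addressed the theme.

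- *k* ranges from max(0, 24 − 25) = 0 to 12.
- Neither low score nor theme: 25 − (12 + 12 − *k*) = 1 + *k*.
- Concordant caregivers (both or neither): *k* + (1 + *k*) = 2*k* + 1, which runs from 1 to 25.

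Identical group summaries are thus compatible with almost no individual agreement and with complete agreement. Other values of *a* and *b* give other ranges. The illustration shows what group totals leave open, not what the study is likely to find.

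**4. How many usable pairs are there?** Three groups of six to eight hold 18 to 24 people, and four hold 24 to 32. If all 25 caregivers joined groups, there would be four groups. The split between groups and individual interviews is not stated. In a group, a caregiver who does not raise a theme has not shown that it is absent. The number of usable pairs for a theme is therefore at most 25, and lower whenever some caregivers do not address it.

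**5. Is coding kept independent of the scores?** Two statements bear on this. One says the strands are analysed separately, which does not say that coding is finished before scores are seen. The other says that biases will be noted and will have no effect. Noting them is useful, but the rest is an assurance with no procedure attached.

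**The case against.** The strongest reply is that a side-by-side comparison is the method the article cites for its convergent design and that it suits the aim of confirming or disconfirming. A joint display is then a preference, and who codes, how many coders there are and in what order may sit in a fuller protocol that is not shown. Much of this stands. Choosing a side-by-side comparison is neither a mistake nor a contradiction, and the number of coders or an agreement check is not missing from a condensed article. What remains is that the article does fix the integration method and its place, and as fixed it makes no stated use of paired data collected for comparison.

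It can also be said that the questionnaires already allow a within-person analysis of quality of life against needs met. That is correct, so the research question does not depend on the integration step alone. The gap lies in linking scores to what caregivers say.

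A reader might infer more than the text supports:

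- **That the within-person link is lost.** Nothing prevents linkage. The link is unused, although focus groups make it harder to attribute statements to a person.
- **That there is no safeguard at all.** Separate analysis and the noting of biases are both stated. They are thin, but they exist.
- **That the facilitator collects or sees the scores, or codes the transcripts with them in hand.** The article says only that he facilitates the interviews and that both data types come from the same session. Coding influenced by scores is a possibility, not something the plan describes.
- **That 25 linked comparisons per theme are available.** Silence in a focus group rules this out for any theme that not everyone addresses.

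**Conclusion.** The point holds as a cheap improvement, not as an error in the plan. Convergence judged from group-level results alone would not show that low quality of life and unmet needs occur in the same caregivers, and its independence would rest on an assurance.

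The size of any coding bias cannot be derived from the article, and neither can the chance of misleading agreement; the range in the working depends on assumed counts. The conclusion rests on two assumptions: that the comparison will be made at the level of results, which is the natural but not the only reading, and that no fuller document already specifies a participant-level link or an order of coding and scoring. If one does, the article need only say so.

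**What to change.** In the last paragraph of Materials and methods, keep the side-by-side comparison but base it on a participant-level joint display reported in the results:

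- One row per participant ID, showing the SF-36 areas, the questionnaire answers on care needs met, and each theme recorded as voiced, contradicted or not raised.
- Concordance counted only among caregivers who addressed the theme, with that denominator shown.
- One-on-one and focus-group participants shown separately.
- Speakers tagged by ID at transcription.
- Theme coding completed and locked before the questionnaires are scored.

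The cost is speaker tagging, a fixed order of analysis steps and one table. Tagging should be arranged before the sessions begin, because untagged group statements may be hard to link to scores later. The drawback is that there will be fewer than 25 usable pairs for any theme not raised by everyone, so the counts should be read as descriptive.
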